## 6.2 Potential Benefits

Regarding the participants, we expect to see a decrease in symptoms related to depression, anxiety and PTSD over time throughout the intervention. Therefore, the main potential benefit to the subjects is an improvement in their mental health. Moreover, since the intervention contemplates “problem solving” and “emotional regulation” components, foreseeable benefits would be improvements in situations that participants identify as problematic, as well as in their capacity to manage distressful emotions. Additionally, since the intervention tackles specific aspects related to migration, such as “migratory grief”, a potential benefit is an improvement in the psychological integration to the host country.

Furthermore, we expect the study to provide knowledge on the efficacy of an intervention specifically tailored to tackled CMD in the population of Venezuelan migrants. As noted above (section 3), no evidence has been generated for the efficacy or CMD interventions that are culturally acceptable and contextually feasible to alleviate anxiety, depression and PTSD among Venezuelan migrants living in Peru, which has received upward 1.5 million migrants from Venezuela. More broadly, we expect the proposed study to provide knowledge about the feasibility and efficacy of a transdiagnostic treatment protocol to target mental health disorders in forcibly displaced populations who have migrated to resource-limited settings. The global prevalence of forcible displacement is estimated to be 70 million per year. While it is difficult to accurately assess the exact burden of disease found in forcibly displaced populations,

Adaptation and assessment of a common element treatment protocol designed to improve mental health in forcibly displaced populations  
Version 1, September 17, 2024  
calculations of mental health prevalence range from approximately 10-30% for depression, anxiety and PTSD.

In the case of the provider participants, we expect that the training leads to the development of skills that will be of help for them in future opportunities.

### 6.3 Analysis of Risks in Relation to Benefits

The population to which the study subjects belong has very limited access to mental health services (see also section 3). Due to bureaucratic barriers, xenophobic attitudes and a lack of resources, Venezuelan migrants are mostly left out of the mental health system provided by the Peruvian State. Furthermore, decreasing availability of funding is jeopardizing the continuity of mental health services provided by NGOs that prioritize migration, as has been informed to us in focus groups with experts. Therefore, mental health interventions specifically tailored for this population that are lay-oriented and strengthen the resources at community and primary care level are promising. With this study we expect to contribute to expand the mental health services provided to Venezuelan migrants in Peru and to put forward a model that could benefit other populations of migrants or forcibly displaced individuals. Furthermore, in relation to the study participants, we expect to provide an intervention that addresses and alleviates their distress in a context, where it would otherwise be left unattended, due to the restrictions mentioned above. Though distress might increase initially, we are basing our intervention in well supported treatment protocols, that have proven their efficacy in numerous studies in different populations. Thus, we expect to overall contribute to the well-being of the subjects.

## 7 Study Subject Selection

### 7.1 Subject Inclusion Criteria

One group of study subjects are outpatient individuals, with symptoms of common mental health disorders, such as anxiety, depression and/or PTSD.

In order to be eligible to participate in this study, an individual must meet all of the following criteria:

- have Venezuelan nationality
- have arrived in Lima in years 2014 to the present
- be 18 years of age or older

In addition, in order to be eligible to participate in this study, an individual must meet ONE of the following criteria:

- score 10 points or more at the PHQ9 or
- score 10 points or more at the GAD7 or
- have a history of trauma exposure as listed in the LEC 5 and score 31 points or more in the PCL5

Another group of study participants are lay providers, who are eligible if the 18 years of age or older.

### 7.2 Subject Exclusion Criteria

Participants with suicidality, homicidality and psychosis will be excluded from the study. An individual is excluded from the study if they endorse suicidal or homicidal thoughts in the past

Adaptation and assessment of a common element treatment protocol designed to improve mental health in forcibly displaced populations  
Version 1, September 17, 2024  
three months, or a lifetime psychosis diagnosis:

- Suicidal ideation: “When someone feels as upset as you do, they may have thoughts that life isn’t worth living. What thoughts have you had like this? Have you had these thoughts in the past three months?”
- Homicidal ideation: “When someone feels as upset as you do, they may have thoughts about hurting the person who has upset or hurt them. What thoughts have you had like this? Have you had these thoughts in the past three months?”
- Psychosis: “Do you have a diagnosis of psychosis or schizophrenia?”

If an individual endorses one of these items they will be referred to relevant care options.

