### 4.2.2 Secondary Outcome Measures

Additionally, the feasibility and acceptability of the intervention will be secondary outcomes. Recruitment rate, reasons for not participating, retention rate, fidelity and acceptability by providers and participants will be measured. Regarding fidelity, the providers will perform an adherence checklist and audio record their sessions. Research staff will assess 20% of the recorded sessions for adherence and competence. Regarding acceptability, providers and participants will complete a participant satisfaction assessment for each session. The following instruments will be used to measure the secondary outcomes:

- Feasibility:
  - o Recruitment:
    - % of participants who consent to screening
    - % who are eligible who enroll
    - characteristics of refusers and reasons for refusal

Adaptation and assessment of a common element treatment protocol designed to improve mental health in forcibly displaced populations

Version 1, September 17, 2024

- % who meet eligibility
- reasons for ineligibility
- % ineligible for each criterion
- Retention:
  - X enrolled who completed all study visits and follow-up assessment
- Fidelity:
  - Adherence scores in provider checklist
  - Adherence and competence scores (0 to 10) from research staff assessment of audio recorded sessions
- Acceptability:
  - Provider perception (assessed after each session):
    - Perception of satisfaction of the participant in the session's helpfulness, enjoyment and relevance (0 to 10)
    - Plans to use material learned in the future (Yes/No)
  - Participant perception (assessed after each session):
    - Direct participant report on the satisfaction in the session's helpfulness, enjoyment and relevance (0 to 10)
    - Plans to use material learned in the future (Yes/No)

Acceptability measures will be collected after each session via a REDCap secure link-sent to each provider and participant by the research team.

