Once this information has been delivered and questions have been clarified, we will collect informed consent for the screening. To this end, participants will receive a secure link to REDCap. Upon consent, participants will be asked questions regarding age, nationality, date of arrival to Peru, suicidality, homicidality, psychosis and the items of the PHQ9, GAD7, LEC5 and PCL5. The researcher will walk the person through the questionnaires during the call, read the questions and mark their answers. If no exclusion and all inclusion criteria apply, individuals will receive a message inviting them to participate in the study. Otherwise, they will be communicated that they cannot be included in the study and information on organizations offering mental health support will be shared with them. If suicidality or homicidality is identified, a safety plan will be implemented. Individuals will be told that their safety is at risk and that we need to contact family member. We will contact a family member and refer to the hospital or other relevant care options, such as the Community Mental Health Centers. Furthermore, individuals will be advised to call the hotline 113 to get in touch with counselors from the Peruvian mental health system.

The Screening Consent Form is attached to this Protocol in a separate document.

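### Section 7.2 excludes a lifetime psychosis diagnosis, but its printed screening question is in the present tense and does not ask about past diagnoses

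*Protocol*

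**What the plan says.** Section 7.2 of the protocol states the exclusion rule in one sentence: "An individual is excluded from the study if they endorse suicidal or homicidal thoughts in the past" "three months, or a lifetime psychosis diagnosis". The sentence ends in a colon, and three questions follow.

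- Psychosis: "Do you have a diagnosis of psychosis or schizophrenia".
- Suicidal ideation: a lead-in telling the person that someone as upset as they are may find that "they may have thoughts that life isn’t worth living".
- Homicidal ideation: a lead-in of the same kind, that "they may have thoughts about hurting the person who has upset or hurt them".

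Both ideation lead-ins are followed by the same probe and time window: "What thoughts have you had like this? Have you had these thoughts in the past three months". Section 7.2 closes by referring anyone who endorses an item for care. Section 10 has the researcher read out the items on a call and record the replies, and adds: "If suicidality or homicidality is identified, a safety plan will be implemented". Section 4.2.2 lists, among the feasibility outcomes, the percentage "ineligible for each criterion".

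**The concern.** A screening question should ask for the period that its criterion names. The rule covers any psychosis diagnosis in the person's life, while the question asks what the person has now. Where the two differ, the question decides who enters, because the screener records the reply to it. In the sections shown, no other screening step asks about psychiatric history.

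What is at stake is mainly safety. A person whom the protocol means to exclude could be treated by a lay provider, and Section 8 suggests exposure to situations or to memories for some score profiles. To a smaller degree, eligibility may be applied unevenly from one screener to the next, and the per-criterion ineligibility figures may carry a label that does not match what was asked.

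**Working it through.** The plan states no figure on this point and no arithmetic applies. The check sets each part of the rule in Section 7.2 against its printed question.

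| Part | Rule | Question | Result |
|---|---|---|---|
| Psychosis, period | Lifetime | Present tense, nothing on the past | Differs; question narrower |
| Suicidal thoughts, period | Three months | Three months | Agrees |
| Homicidal thoughts, period | Three months | Three months | Agrees |
| Suicidal thoughts, content | Suicidal | Lead-in on life not being worth living, then open probe | Lead-in broader; probe can draw out the rule's content |
| Homicidal thoughts, content | Homicidal | Lead-in on hurting someone, then open probe | Lead-in broader; probe can draw out the rule's content |

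**Psychosis, followed through.**

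1. Take a person with a past diagnosis who considers it resolved. Under the rule sentence, that person is excluded.
2. Asked whether they have such a diagnosis, they can truthfully say no.
3. Under Section 10, a person with no exclusion recorded and the inclusion criteria met is invited to take part.
4. Under Section 8, exposure to situations is suggested at GAD7 of 10 or more and exposure to memories at PCL5 of 31 or more. These thresholds also appear among the entry routes in Section 7.1. Exposure is therefore possible for such a person but not certain: someone who qualifies on PHQ9 alone would not be steered to either component in the symptom-focused phase.

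**Ideation items, followed through.** The protocol names three consequences with three different triggers.

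- Exclusion follows from endorsing suicidal or homicidal thoughts (7.2, rule sentence).
- Referral follows from endorsing an item (7.2, closing sentence).
- The safety plan, which includes contacting a family member, follows from suicidality or homicidality being identified (Section 10).

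No section shown says how the answer to the open probe is graded. If a person reports only that life has not felt worth living, two screeners could classify the reply differently and both would be within the protocol.

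**Effect on the feasibility outcomes in Section 4.2.2.** Consent to screening comes before these questions. The share of eligible people who enrol is conditional on having passed them. What could be affected is the share meeting eligibility, the reasons for ineligibility and the per-criterion percentages.

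**The case against.** The strongest reply on psychosis is that asking whether someone has a diagnosis can naturally cover any diagnosis ever given, and that the rule sentence just above it says lifetime. Section 14.2 also lists a separate psychosis form in an appendix that is not shown, and Section 11 has the study explained in Spanish, so the words actually spoken may differ. Section 8 provides referral if psychosis becomes apparent during treatment. All of this lowers the likely harm, but it does not remove the mismatch. The wider reading is available but not forced, and a differently worded form would itself conflict with 7.2.

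On the ideation items the reply is stronger. A reader might infer that none of the three questions asks what its rule states, and that otherwise eligible, more distressed people are being turned away. The documents do not support that. The three-month window is asked as the rule has it, and the open probe gives the interviewer a way to reach suicidal or homicidal content. The questions follow a colon and can be read as the working definition of the criterion, perhaps with deliberate caution. Endorsing an item is tied expressly only to referral. No section says that a reply limited to passive thoughts, or to thoughts of lesser harm, excludes anyone. What stands is narrower: which answers count is not defined.

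A reader might also infer damage to the trial's inference. Screening comes before randomisation, so any effect of the wording falls on both arms alike.

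**Conclusion.** The psychosis point holds: rule and printed question in Section 7.2 differ in the period they cover, and the difference can let in a person the protocol means to exclude. This rests on reading the question literally and on the printed wording being what is asked.

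The ideation point holds only as a secondary one. The lead-ins are broader than the rule's terms and the triggers in 7.2 and Section 10 are not aligned, so the passages need reconciling. The documents do not show that anyone is wrongly turned away.

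No size can be put on either point, because the documents give no rate of past psychosis diagnosis or of the thoughts elicited. Sample size, alpha and the primary comparison are unaffected. The psychosis item is worth correcting because its consequence is one of safety and the correction is simple. Which exclusion rule is clinically right is for the investigators.

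**What to change.** 1. Reconcile the psychosis rule and question in Section 7.2 and on the screening form, including its Spanish wording, so that the question asks for the period the rule states. If lifetime is intended, ask whether the person has ever been given such a diagnosis. If it is not, the rule sentence should change instead.
2. For the two ideation items, state which answers to the open probe count for exclusion, for referral and for the safety plan, and align Section 7.2 with Section 10. Either the criterion or the question may be reworded; that choice is the investigators'.
3. Record the thought elicited separately from the judgement that a criterion is met, so that the per-criterion percentages in Section 4.2.2 report what was asked.

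The cost is rewording one screening item, a short clarification for the other two, one REDCap field and an IRB amendment. No extra visits or staff are needed.

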## 8 Study Intervention

The intervention in the present study was developed based on CBT techniques that have proven effective in the treatment of CMD. The intervention underwent a process of cultural adaptation following the Ecological Validity Model developed by Bernal et al. (1995), which has been used in numerous adaptations of psychosocial interventions, for instance by Perera et al. (2020 and 2022) in the adaptation of Problem Management Plus for its implementation with Venezuelan migrants in Colombia. In the following paragraphs we describe the intervention that resulted from this process. Figure 1 synthesizes its components:

[figure not shown]

Figure 1. Intervention components and implementation strategies.

In terms of the implementation, the intervention will be free of cost for the participant. It will comprise between 6 and 12 weekly sessions in consecutive weeks and will be delivered remotely via a video call. The sessions will last 60 minutes and before each session participants will be sent a link to REDCap to fill out the questionnaires for the measurement of the primary outcomes. After the session they will answer questions on the session’s acceptability. Since it has been identified that Venezuelan migrants have long working days and might also work in the weekends, we will offer many possibilities to schedule the sessions (e.g. Sundays, early in the morning, late at night...). There will be some flexibility will sessions cancellations and re-scheduling. However, at the beginning of the intervention some rules in this regard will be

Adaptation and assessment of a common element treatment protocol designed to improve mental health in forcibly displaced populations  
 Version 1, September 17, 2024  
 agreed upon between provider and participant. A general rule will be set in place and participants will be told that if they can re-schedule a maximum of three sessions in a row and of six sessions overall throughout the intervention. Otherwise, they will be excluded from the study

Regarding the providers, they will receive an intensive in-person two-week training followed by weekly supervisions with their peers. Following the apprenticeship model, 2-3 providers who are identified as “very competent” in the training will assume the role of lay provider supervisors. Lay provider supervisors will be closely supervised by professionally trained counselors (research staff, the US equivalent of bachelors level psychology training or higher) who will in turn be supervised by the primary investigator. Supervision will take place weekly. Competence of providers, lay person supervisors, and supervisors will take place continuously during supervision and be addressed via supervision feedback. This will provide with opportunities to assess any risks and the need to put into action the safety plan, but also to make sound decisions regarding the intervention components based on the information shared in the weekly supervisions and to provide timely support in the implementation of the intervention strategies. Furthermore, providers will have a manual describing each session and the strategies. This material has been written and designed, so that both provider and participant can look at it at the same time. A network of organizations active in mental health and migration will be set in place for providers to make referrals, both as part of the strategies (e.g. a list of organizations that offer community activities for the strategy “behavioral activation”) as well as in case of increasing severity or suicidality, homicidality or psychosis (e.g. community mental health centers in the participant’s neighborhood, organizations that provide support to the victims of domestic violence).

In the intervention itself we have identified via prior interviews that there is a prevalent belief that talking about distress can make it worse and interfere with the possibility of “keep going” to make a daily living, fulfill family duties and accomplish the goals that Venezuelan migrants have set for themselves. Taking this belief into consideration, the intervention begins with an **orientation session**, in which the purpose of the intervention is communicated in terms that make sense for the participant, feedback is provided from the initial assessment and the migratory experience, current difficulties and goals of the participant are explored empathically. Accordingly, the relevant components of the intervention will be briefly presented to the participant, agreed upon and calendarized. This aims to foster an atmosphere of warmth, horizontality and cooperation, which Venezuelan migrants have indicated in interviews is culturally expected.

The **next 3 to 7 sessions** will then tackle the most urgent symptoms identified and discussed with the participants. In an exercise of hope building, the therapist will communicate to the participant that the components presented have shown efficacy in providing relief in people with similar distress. The following components will be suggested in this phase of the intervention:

| Component                | Suggested if      |
|--------------------------|-------------------|
| Cognitive re-structuring | Always            |
| Behavioral activation    | PHQ9 => 10 points |
| Exposure to situations   | GAD7 => 10 points |

|                      |                   |
|----------------------|-------------------|
| Exposure to memories | PCL5 => 31 points |
|----------------------|-------------------|

Here a dosage of the intervention occurs according to the present symptoms. In the case of participants that score higher than the cut-off in all three of the questionnaires applied, more sessions will be dedicated to strategies that tackled symptoms. For participants with a less complex symptomatology, less sessions will be dedicated to this. Once the strategies above have been implemented, participants can opt to continue with **a supplementary set of sessions** (to reach a total of 12 maximum) that may comprise the following components:

| Component            | Suggested if                                                                                                                                                                                                                                                                                                                           |
|----------------------|----------------------------------------------------------------------------------------------------------------------------------------------------------------------------------------------------------------------------------------------------------------------------------------------------------------------------------------|
| Emotional regulation | Participant describes difficulties identifying, managing and expression emotions (e.g. sudden outbursts of rage, emotional build-up and sudden crying, impulsivity)                                                                                                                                                                    |
| Problem solving      | Participant describes concrete circumstances that generate stress and feels urgent to change (e.g. unemployment, poor housing conditions, lack of support with childcare, etc) and mention feeling stuck or paralyzed regarding their problems, not being able to make a plan, feeling overwhelmed by decisions they should be making. |
| Adaptation focus     | Participant describes difficulties in feeling “at home” in the host country (e.g. feeling “out of place”, fear of losing the Venezuelan identity, distrusting and avoiding Peruvians, etc).                                                                                                                                            |

In the following table we will briefly describe each of the components. Each component comes with a “homework” to put into practice in the time between sessions:

| Component                | Brief description                                                                                                                                                                                                                                                                                                                                                  |
|--------------------------|--------------------------------------------------------------------------------------------------------------------------------------------------------------------------------------------------------------------------------------------------------------------------------------------------------------------------------------------------------------------|
| Cognitive re-structuring | This is a strategy used in the treatment of different mental disorders. It introduces the triangle “thought-emotion-action” and explores how these three aspects influence each other. Participants examine how a thought can impact the way they feel and their actions. They learn how to “opt” for more helpful thoughts.                                       |
| Behavioral activation    | This is a strategy commonly used in the treatment of depression. It introduces the idea that action can precede motivation and not (only) the other way around. Participants are invited to engage in pleasurable activities, which are disaggregated in small and feasible steps.                                                                                 |
| Exposure to situations   | This is a strategy used in the treatment of different forms of anxiety. Participants learn that anxiety often leads to avoidant behaviors that exacerbate the distress in a spiral of isolation. By means of facing the dreaded (but harmless situations) gradually, they learn that they can overcome anxious feelings and are able to engage in more activities. |

|                      |                                                                                                                                                                                                                                                                                                                                                                                                                                                                                                                                                                                                                                                                                                                                                                                                                                                                                                                                                                                                                                                                                                                                                                                                                                                                   |
|----------------------|-------------------------------------------------------------------------------------------------------------------------------------------------------------------------------------------------------------------------------------------------------------------------------------------------------------------------------------------------------------------------------------------------------------------------------------------------------------------------------------------------------------------------------------------------------------------------------------------------------------------------------------------------------------------------------------------------------------------------------------------------------------------------------------------------------------------------------------------------------------------------------------------------------------------------------------------------------------------------------------------------------------------------------------------------------------------------------------------------------------------------------------------------------------------------------------------------------------------------------------------------------------------|
| Exposure to memories | This is a strategy used in the treatment of PTSD. There is often concern that intentionally approaching memories that trigger distress will exacerbate symptoms. Participants learn that the avoidance of these triggers is likely what maintains the intrusive memories, which is harmful. They intentionally evoke the memories that provoke the distress and re-learn that these are not dangerous, that they can overcome the distress, and that they will experience less distress over time.                                                                                                                                                                                                                                                                                                                                                                                                                                                                                                                                                                                                                                                                                                                                                                |
| Emotional regulation | Participants learn to identify, name and communicate uncomfortable emotions. They also examine their coping strategies, when feeling emotionally overwhelmed, critically assess them in terms of their advantages and disadvantages and expand their repertoire.                                                                                                                                                                                                                                                                                                                                                                                                                                                                                                                                                                                                                                                                                                                                                                                                                                                                                                                                                                                                  |
| Problem solving      | Participants learn a method to solve problems. They list their most urgent problems, choose one, describe it in detail, gather solutions, select the most feasible strategies and put together an action plan.                                                                                                                                                                                                                                                                                                                                                                                                                                                                                                                                                                                                                                                                                                                                                                                                                                                                                                                                                                                                                                                    |
| Adaptation focus     | Participants focus on feelings related to having migrated to put into action the strategies mentioned above, but this time with an emphasis on supporting their adaptation to the host country. For instance, participants use the strategy “cognitive re-structuring” to examine the way they feel about having migrated, identify common thoughts related to this and practice new and more helpful ways to think about the place they now live in. Or participants use “behavioral activation” to put into action small changes that might enhance the pleasurable feeling of “being at home” in their “new homes”. Or participants plan an activity with Peruvians (e.g. colleagues, neighbors, parents of their children’s friends), if they tend to avoid hanging out with Peruvians (exposure to situations). Or participants remember the most painful or distressful parts of the experience of having migrated like separating from their children, facing difficulties during the journey or upon arrival (exposure to memories). In terms of emotional regulation, they learn to oscillate between the grief-like feelings and past-focused cognitions and the implementation of healthy coping strategies and present- and future-oriented thinking. |

The **last session** allocates time to review the process and to make a plan to continue to put into practice the strategies learned. It also includes a discussion of possibility of relapse and strategies to prevent it or recover from it.

